### Intervention and control condition

Prior to intervention, baseline data will be collected including demographics, medical characteristics, assessment of chemotherapy-induced hair loss, facial color, thumbnail color, grading of thumbnails ridging, quality of life, blood routine test results, and hepatic and renal function. After that, subjects assigned to group A will receive YH0618 granules three times a day (6 g each time), 6 days a week, mixed with 300 ml warm water from the first to the fourth chemotherapy cycle. Subjects in group B will receive the placebo granule in the same manner. Then, all the subjects will be followed up for 1 month after chemotherapy. All specific methods, such as scalp cooling, used for reducing hair loss will be prohibited during the clinical trial. Both YH0618 granules and placebo are produced by Guangzhou Kanghe Pharmaceutical Co., Ltd., which meets national standards.

### Outcome evaluation

#### Primary outcome

The primary outcome is the time point of occurrence of hair loss reaching grade II as assessed by the WHO Toxicity Grading Scale, and objective indices of hair quality and hair-follicle growth recorded by a hair and scalp detector (CBS-603, CBS, Taiwan) before the fifth chemotherapy cycle.

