### Estimation of sample size

The primary outcome in this study is the time point of occurrence of chemotherapy-induced hair loss reaching grade II measured by the WHO Toxicity Grading Scale for Determining the Severity of Adverse Events. Our previous results showed that YH0618 could cause the incidence of hair loss grade < II to reach 50% for patients who have completed chemotherapy, and the difference between the incidence of hair loss grade < II in YH0618 group and the control group was 15%. Thus, the difference in proportion between the two groups will be measured by a Z test. To achieve a two-sided, type-I error alpha = 0.05 and power: (1 − beta) = 80%, the minimal number of subject need in each group is 85. We estimated a 20% attrition rate at the end of follow-up; hence, a sample size of at least 107 in each group (214 in total) is planned for this study.

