### Grading of chemotherapy-induced hair loss

The WHO Toxicity Grading Scale is commonly used to monitor and rate the severity of anticancer drug-induced toxicity [19, 20]. The grading criteria for hair loss is shown in Table 2. Alopecia assessments will be conducted by a clinician blinded to treatment assignment, and by the participant.

**Table 2 Tab2:** World Health Organization (WHO) grading criteria for anti-drug induced hair loss

Grade 0	No hair loss
Grade I	Minor hair loss
Grade II	Moderate hair loss/alopecia areata
Grade III	Complete hair loss with regrowth
Grade IV	Non-regrowth hair loss

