#### Objective measurement of hair loss

In order to objectively evaluate the hair quality and hair-follicle growth, a hair and scalp detector (CBS-603) will be used. The detector obtained patents in the United States, German, Japan, China, and China Taiwan, and many international authentications from Conformité Européenne (CE), Federal Communications Commission (FCC), and Restriction of Hazardous Substances (RHoS). The detector is composed of a 10X-200X Hair and Scalp Camera and software. The whole top of the head, a wide range of hair loss and the condition of hair follicles could be clearly filmed at 10X, 50X and 200X, respectively. The software has a function of testing through which hair testing and analysis can be conducted. In this study, identification and classification of the level of hair loss, hair diameter and quality will be analyzed.

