### Statistical analysis

All analyses will be performed based on intention-to-treat principles, any missing data in the follow-up visits will be imputed using multiple imputation. Descriptive analyses as means and standard deviations (SDs) will be used to describe the demographics and clinical characteristics of the participants. The primary efficacy analysis compared the hair-loss grading between YH0618 granule and control before the fifth chemotherapy using Fisher’s exact test. The changes of hair diameter between the two groups after four cycles of chemotherapy will be compared by an independent samples *t* test. A multivariable logistic regression model will be used to explore the treatment effect. Potential confounding variables will be identified as those that differ among treatment groups at baseline and are significantly associated with outcomes. Changes from baseline to the final assessment in quality of life assessed by the FACT-B and objective indicators in the blood will be compared using Wilcoxon rank sum tests. Unless otherwise specified, two-sided statistical tests will be used and the significance level will be set at *p* < 0.05.

In this trial, an interim analysis will be performed when approximately two thirds of the planned observations are enrolled. The results are analyzed by the statistician and only DSMB members have access to the results to test for futility, safety and efficacy of the trial. A predefined stopping rule will be applied to the data to determine whether it is futile to continue enrollment.

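### The protocol calls several outcomes primary in four places and one in two others; if a hair-diameter result alone could count as primary success, the false-positive rate is about 7% to 9.75%

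*Protocol article*

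**What the plan says.** Four places in the protocol article give more than one primary outcome. The Abstract, Study design and Primary outcome sections each name the time at which hair loss reaches WHO grade II and then add "and objective indices of hair quality and hair-follicle growth recorded by a hair and scalp detector" or near-identical wording. Table 1 puts the grade and the objective indices in separate rows, both under primary outcomes. The section Objective measurement of hair loss indicates what the indices cover: "identification and classification of the level of hair loss, hair diameter and quality will be analyzed".

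Two places give only one. Estimation of sample size opens with "The primary outcome in this study is the time point of occurrence of chemotherapy-induced hair loss reaching grade II" and mentions no detector index. Statistical analysis says "The primary efficacy analysis compared the hair-loss grading between YH0618 granule and control before the fifth chemotherapy", using Fisher's exact test.

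Statistical analysis then turns to one detector index, without the primary label: "The changes of hair diameter between the two groups after four cycles of chemotherapy will be compared by an independent samples" *t* test. The general rule at the end of that paragraph is "Unless otherwise specified, two-sided statistical tests will be used and the significance level will be set at" *p* < 0.05. Nothing in the section sets an order of testing, divides the 0.05, or says whether one or all of the primary outcomes must be positive.

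The grade itself has two sources: "Alopecia assessments will be conducted by a clinician blinded to treatment assignment, and by the participant". The protocol does not say which of the two scores is the primary one.

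**The concern.** The identity of the primary outcome decides what may be reported as a positive trial, and here the reader gets two answers. Suppose the grade comparison is null and the hair-diameter comparison gives *p* = 0.03. Under the Primary outcome section and Table 1, the authors could report a positive primary outcome. Under the sample-size and Statistical analysis sections, the trial has failed on its primary analysis. Both reports would be faithful to the protocol. If the choice can be made after the data are seen, the 5% error rate is not protected.

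**Working it through.** **1. Which outcome the sample size belongs to.** The plan gives no error rate for its primary claim, so there is none to reproduce. Its one related figure is 85 per group. The inputs, all from Estimation of sample size, are 50% with grade below II on YH0618, a difference of 15 points (so 35% on control), a *Z* test of proportions, two-sided alpha 0.05 and power 80%. For two proportions:

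n per group = [z(0.975)·√(2p̄(1−p̄)) + z(0.80)·√(p₁(1−p₁) + p₂(1−p₂))]² / (p₁−p₂)²

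With p₁ = 0.50, p₂ = 0.35 and p̄ = 0.425 this is (1.960 × 0.699 + 0.842 × 0.691)² / 0.0225 = 3.81 / 0.0225 = 169.3, so 170 per group. The stated 85 is not reproduced; it is half of 170. The attrition step does reproduce: 85 / 0.80 = 106.25, so 107. The shortfall is a separate matter. What counts here is that the calculation concerns a binary grade, below II versus II or above. It is neither a time to event nor a detector index.

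**2. How many primary tests the protocol names.**

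| Variable called primary somewhere | Test named in Statistical analysis | Labelled as the primary analysis |
|---|---|---|
| WHO hair-loss grade before cycle 5 | Fisher's exact | yes |
| Hair diameter | independent-samples *t* | no |
| Detector level of hair loss | none | no |
| Detector hair quality | none | no |
| Time to grade II | none | no |

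The count that rests on the text is therefore two.

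**3. Error rate if either of the two suffices.** For k independent tests at 0.05 the chance of at least one false positive is 1 − 0.95^k. For k = 2 this is 1 − 0.9025 = 9.75%.

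Grade and diameter come from the same scalp, so independence is an upper case. The protocol gives no correlation, so a range is assumed. Simulating P(|Z₁| > 1.96 or |Z₂| > 1.96) with 1,000,000 draws gives:

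| Assumed correlation | At least one false positive |
|---|---|
| 0 | 9.7% (agrees with the formula) |
| 0.3 | 9.5% |
| 0.5 | 9.1% |
| 0.8 | 7.8% |
| 0.9 | 7.0% |

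**4. Error rate under the other two rules.** If only the labelled grade comparison counts, the rate is at most 5%. If all must succeed, it is also at most 5%, because a joint false positive cannot be more frequent than a false positive on one test alone.

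**The case against.** The best defence is that the protocol does rank its outcomes. It sizes the trial on the hair-loss grade only and reserves the primary label in the Statistical analysis section for the grade comparison; hair diameter follows without it. On that reading the error rate is at most 5% and the outcome lists are merely loosely worded. A detailed multiplicity rule may also sit in an analysis plan that is not shown.

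Much of this stands. It would be wrong to say that the protocol has no hierarchy, or that inflation is certain. Inflation arises only if any one outcome suffices, which the text neither states nor excludes. An absent multiplicity rule would not by itself be a finding.

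What does not fall away is the contradiction. Sizing on one outcome does not demote the others, and the indices carry the primary label in four places, including the section whose purpose is to define the primary outcome. An analysis plan can add detail, but this document would still give two answers.

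A reader might go further and count every index and both raters as separate tests at 0.05, which gives 14.3% for three tests, 18.5% for four and 22.6% for five. The document does not support this. It names no test for detector hair-loss level, for quality or for the participant's grade. Those figures also treat two raters grading the same head as independent.

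A reader might equally take time to grade II as the outcome on which the trial is sized. The sample-size section uses that label, but its arithmetic compares two proportions, and the analysis looks at grade at one visit.

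**Conclusion.** The concern holds as an inconsistency about what is primary. Four places name the grade outcome plus detector indices; two name the grade alone; no success rule settles it. For the two tests actually named, the chance of a false primary claim is 9.75% if independent and about 9.1% to 7.0% at correlations of 0.5 to 0.9, **provided either result could be claimed**. It stays at or below 5% if only the labelled analysis counts or if all must succeed.

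The figures assume that each test has a true size of 5%, and the correlations are assumed. Fisher's exact test is usually conservative, which would lower the figures somewhat. Any error added by the planned interim look is left out.

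**What to change.** Name one primary outcome, in the same words, in the Abstract, Study design, Table 1, Estimation of sample size, Primary outcome and Statistical analysis: the WHO hair-loss grade before the fifth cycle, as below II versus II or above, scored by the blinded clinician. This matches both the sample-size calculation and the labelled primary analysis. If a time-to-grade-II outcome is preferred, the sample size and the analysis must both be changed to fit it.

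Make the detector indices key secondary outcomes, tested in a prespecified fixed order and only if the primary is significant. Start with hair diameter, the only index with a named test, and name a test for each further index that is kept in the sequence. Treat the participant's grade as supportive. Choosing the clinician's score is a judgement, since participants are blinded too; the essential step is to fix one of them.

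Settle this before the interim analysis, which is to test efficacy.

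**Cost:** wording in six places. The indices lose the primary label, and a significant diameter result after a null grade result could no longer be claimed as confirmatory. No patients or data are lost, and the fixed order needs no extra patients. Keeping two co-equal primaries at 0.025 each would cost more: for 50% versus 35%, 206 per group instead of 170 before attrition. At the planned 85 per group, power on the grade would drop from 51% to 39%.

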### Grading of chemotherapy-induced hair loss

The WHO Toxicity Grading Scale is commonly used to monitor and rate the severity of anticancer drug-induced toxicity [19, 20]. The grading criteria for hair loss is shown in Table 2. Alopecia assessments will be conducted by a clinician blinded to treatment assignment, and by the participant.

**Table 2 Tab2:** World Health Organization (WHO) grading criteria for anti-drug induced hair loss

Grade 0	No hair loss
Grade I	Minor hair loss
Grade II	Moderate hair loss/alopecia areata
Grade III	Complete hair loss with regrowth
Grade IV	Non-regrowth hair loss

#### Objective measurement of hair loss

In order to objectively evaluate the hair quality and hair-follicle growth, a hair and scalp detector (CBS-603) will be used. The detector obtained patents in the United States, German, Japan, China, and China Taiwan, and many international authentications from Conformité Européenne (CE), Federal Communications Commission (FCC), and Restriction of Hazardous Substances (RHoS). The detector is composed of a 10X-200X Hair and Scalp Camera and software. The whole top of the head, a wide range of hair loss and the condition of hair follicles could be clearly filmed at 10X, 50X and 200X, respectively. The software has a function of testing through which hair testing and analysis can be conducted. In this study, identification and classification of the level of hair loss, hair diameter and quality will be analyzed.

### Secondary outcomes

Secondary outcomes include changes of facial color and thumbnail color, grading of thumbnail ridging, assessment of quality life, fatigue level, routine blood test results, hepatic and renal function, and certain medical indicators which can reflect kidney deficiency in Chinese Medicine.

#### Facial color and thumbnail color

The assessment of facial and thumbnail color is performed using the L*a*b system, which is the same as for the clinical trial that we conducted previously [13]. In the fixed surroundings, the skin color of the forehead, right and left cheeks, and jaw, and the thumbnail color will be recorded by the hair and scalp detector at 50X.

#### Grading of thumbnail ridging

The grading of left and right thumbnail ridging will be measured by the National Cancer Institute Common Terminology Criteria for Adverse Events (NCI CTCAE). The definition of nail ridging is a disorder characterized by vertical or horizontal ridges on the nails. The grading criteria for nail ridging is shown in Table 3.

**Table 3 Tab3:** Criteria for assessing chemotherapy-induced nail ridging

Grade 1	Asymptomatic; clinical or diagnostic observations only; intervention not indicated
Grade 2	Distortion of nail shape; associated psychosocial impact

Definition of nail ridging: a disorder characterized by vertical or horizontal ridges on the nails

#### Quality of life measurement

Quality of life has been regarded as an important index to measure and monitor cancer patients’ treatment outcomes [21]. The Chinese version of the Functional Assessment of Cancer Therapy-Breast Cancer (FACT-B) with good reliability and validity will be used to measure breast-cancer-specific quality of life [22]. The tool includes 37 items scored on a 5-point Likert scale, ranging from 0 to 4 with higher scores indicating better quality of life [23, 24]. The items are classified into five subscales: Physical Well-Being, Social/Family Well-Being, Emotional Well-Being and Functional Well-Being, which constitute the FACT-General, and the additional concern for breast cancer, which is called the Breast Cancer Subscale. A total score is calculated by summing all subscale scores.

#### Fatigue measurement

Fatigue will be measured by the Chinese version of FACIT-Fatigue version 4, a 13-item FACIT Fatigue Scale, which could be used for patients with any tumor type [25]. Each item scored on a 5-point Likert self-report scale, ranging from 0 to 4. A total score is obtained by summing all item scores and a high score indicates less fatigue.

#### Clinical objective examination

Routine blood tests and assessment of liver and kidney function are the same as in our previous trial [13]. Based on the evaluation standard of kidney deficiency in Chinese Medicine, kidney deficiency will be divided into deficiency of kidney *qi*, deficiency of kidney *yang* and deficiency of kidney *yin*. Modern studies also found that kidney deficiency syndrome has a modern pathophysiological basis, clinically manifested as changes in the relevant medical indicators such as the adrenal axis, thyroid axis, gonadal axis, renin-angiotensin system, immune energy, liver and kidney function and hematopoietic function [26]. So, in this study, immune indices include immunoglobulin M (IgM), alexin C3, helper T cells CD4+, CD8+ T cells and certain metabolic indices of microelements such as Mg^2+^, Cu^2+^, Zn^2+^, and Fe^3+^.

All participants will be assessed within 3 days before every chemotherapy cycle from the first to the fifth cycle. Then, all the subjects will be followed up and the final assessment will be conducted at 1 month after the last chemotherapy cycle. A professional research assistant will assign YH0618 granules or placebo, and notify the subjects of dosage and time. Quality and compliance to the intervention will be achieved by checking attendance records and the self-record diary kept by each participant.

### Adverse events

Adverse events will be recorded spontaneously through self-reports by participants or asking the participants the open-ended question “How are you feeling?” via phone or face to face. Any questions concerning adverse events will be reported regardless of whether they were deemed to be related to the treatment be assessors and will be sent to the Institutional Review Board of every clinical center.

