**Fig. 1 Fig1:**
[figure not shown]
Flow chart of the clinical trial

**Table 1 Tab1:** Trial process chart

	Before baseline screening	Baseline	Visit 1 treatment phase	Visit 2 treatment phase	Visit 3 treatment phase	Visit 4 treatment phase	Visit 5 follow-up phase
		(before chemo)	Before 2nd chemo	Before 3rd chemo	Before 4th chemo	Before 5th chemo	1 month after chemo
Patients							
Inclusion and exclusion criteria	×						
Informed consent		×					
Demographics		×					
Medical characteristics	×	×	×	×	×	×	×
Randomization and allocation concealment		×					
Primary outcomes							
Grading of hair loss		×	×	×	×	×	×
Objective indices (hair quality and hair follicles)		×	×	×	×	×	×
Secondary outcomes							
Facial color and thumbnail color		×	×	×	×	×	×
Grading of thumbnail ridging		×	×	×	×	×	×
Quality of life and fatigue		×	×	×	×	×	×
Routine blood test		×	×	×	×	×	×
Liver function (ALT, AST, total protein, and Alba)		×	×	×	×	×	×
Renal function (Cr, UA and BUN)		×	×	×	×	×	×
Kidney deficiency (IgM, C3、CD4 +, CD8 + Mg^2+^, Cu^2+^, Zn^2+^, Fe^3+^)		×		×		×	
Adverse events			×	×	×	×	×
Patients’ diary records			Every day during the study				

*BUN* blood urea nitrogen, *Cr* creatinine, *ALT* alanine aminotransferase, *AST* aspartate aminotransferase

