## Discussion

Chemotherapy-induced hair loss occurs usually due to the high mitotic rate of hair follicles instead of a non-androgenic mechanism, and can manifest as alopecia totalis, telogen effluvium, or, less often, as alopecia areata [27]. Severe hair loss occurs most often with drugs such as doxorubicin, daunorubicin, docetaxel, paclitaxel, cyclophosphamide and etoposide, which are common chemotherapy agents used for breast cancer patients. Even some standard chemotherapy regimens can induce permanent thinning or hair loss. Although scalp-cooling is a method approved by the FDA for preventing both permanent and temporary hair loss, concerns about this method have been raised [6, 28]. Therefore, this is the first strict randomized, double-blind, multi-center controlled trial to evaluate the effect of a medicinal and edible compound prescription on chemotherapy-induced hair loss. The proposed study may provide direct and convincing evidence to support YH0618 as an adjuvant treatment for reducing chemotherapy-induced toxicity, which could be introduced into clinical settings. Our achievements will provide a safe and effective way for reducing chemotherapy-induced hair loss and improving patients’ quality of life.

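### Symptom-free laboratory toxicity has no stated route to being counted: adverse events come from self-report or an open question, and the one stated blood comparison is a rank test at a visit weeks after the granules stop

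*Protocol article*

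**What the plan says.** **Capture.** The Adverse events section gives two routes: "Adverse events will be recorded spontaneously through self-reports by participants or asking the participants the open-ended question" of how they feel, by phone or in person. It adds that "Any questions concerning adverse events will be reported regardless of whether they were deemed to be related to the treatment". It gives no grading scale and no rule that turns an abnormal test result into an event.

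**Collection.** Table 1 schedules routine blood tests, liver function ("Liver function (ALT, AST, total protein, and Alba" in the table's wording) and renal function (Cr, UA, BUN) at baseline, at Visits 1–4 and at follow-up. The Secondary outcomes section lists them as secondary outcomes.

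**Analysis.** The Statistical analysis section takes "Changes from baseline to the final assessment in quality of life assessed by the FACT-B" together with the blood results, and says that "objective indicators in the blood will be compared using Wilcoxon rank sum tests".

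**Timing.** Under Clinical objective examination, "the final assessment will be conducted at 1 month after the last chemotherapy cycle". The Subjects section requires at least six three-week cycles. Under Intervention and control condition, granules are taken "from the first to the fourth chemotherapy cycle".

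**Conclusion in view.** The Discussion states: "Our achievements will provide a safe and effective way for reducing chemotherapy-induced hair loss".

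**The concern.** Organ toxicity from an added oral product would typically be strong in a minority of patients and slight or absent in the rest, and it can be silent. The capture rule depends on what a patient notices and says. The stated comparison looks for a general shift between arms, at a time when the product has long been stopped.

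Followed as written, the trial could report no difference in hepatic and renal function and few adverse events while some patients on the product had marked abnormalities during treatment. The Discussion's statement about safety would then rest on rules that were not able to contradict it. The data that could do so are already scheduled.

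**Working it through.** The document gives no laboratory toxicity rate and no power figure for this comparison, so there is no figure of the plan to reproduce here. The affected fractions below are assumptions, shown as a range.

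**1. Which values enter the comparison**

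Count days from the first dose of cycle 1, with 21-day cycles.
- Cycle 4 starts on day 3 × 21 = 63 and ends on day 84. Granules stop by then.
- Cycle 6, the earliest possible last cycle, starts on day 5 × 21 = 105.
- One month (30 days) after day 105 is day 135. Counted from the end of cycle 6 it would be day 156.
- Gap from the last granules: at least 135 − 84 = 51 days, about seven weeks. It is longer with more cycles.

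Visits 1–4 (before cycles 2 to 5) carry the on-treatment values. None of them enters a change from baseline to the final assessment. An abnormality that resolves within seven weeks would leave no trace in the stated comparison.

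**2. Power of the rank test when a few patients are affected**

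Group sizes come from Estimation of sample size: 85 per arm completing, and 107 randomised after 20% attrition (85 / 0.8 = 106.25, rounded up). Whether 85 suits the primary outcome is a separate matter.

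Suppose k of n patients in the product arm move above everyone else and the arms are otherwise alike. With f = k/n:
- P(A > B) = 0.5 + f/2
- standard error = √[(2n + 1)/(12n²)]
- expected z = (f/2)/standard error

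| n per arm | k | P(A > B) | expected z |
|---|---|---|---|
| 85 | 5 | 0.529 | 0.66 |
| 85 | 8 | 0.547 | 1.06 |
| 107 | 5 | 0.523 | 0.59 |
| 107 | 8 | 0.537 | 0.94 |

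All are far below 1.96. Once a patient ranks at the top, a larger elevation adds nothing.

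Simulation: 4,000 trials per case, standard normal changes, +10 SD in a random fraction f of the product arm, none on placebo, two-sided 0.05. It assumes, generously, that the abnormality is present at the analysed visit. Fisher's exact test compares the counts of affected patients.

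| f | Rank sum, n = 85 | Fisher, n = 85 | Rank sum, n = 107 | Fisher, n = 107 |
|---|---|---|---|---|
| 3% | 0.06 | 0.04 | 0.07 | 0.10 |
| 5% | 0.08–0.09 | 0.25 | 0.10 | 0.46 |
| 8% | 0.14–0.15 | 0.68 | 0.18 | 0.86 |
| 10% | 0.20 | 0.87 | 0.25 | 0.96 |

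The ranges in the rank-sum column are repeat runs, which differ by simulation error. With 5% affected, the rank test finds the problem little more often than its 5% false-positive rate. A per-patient table would contain at least one such case with probability 1 − (1 − 0.05)^85 = 0.987.

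**3. The same comparison when chemotherapy causes abnormalities in both arms**

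n = 85 per arm. The background rates are again assumptions.

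| Background in both arms | Excess on product | Fisher on counts | Rank sum |
|---|---|---|---|
| 0% | 5 points | 0.25 | 0.09 |
| 10% | 5 points | 0.12 | 0.08–0.09 |
| 20% | 5 points | 0.08–0.09 | 0.08–0.09 |
| 30% | 5 points | 0.08 | 0.08–0.09 |
| 20% | 10 points | 0.27 | 0.21 |

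At a 20% background and a 5-point excess the expected counts are about 21 against 17 (85 × 0.25 and 85 × 0.20). A table would not make that plain. The power advantage of counting patients is therefore confined to abnormalities that are rare on placebo.

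**The case against.** **Silence is not exclusion.** A journal article condenses a fuller protocol, and laboratory shift tables commonly sit in an analysis plan that is not shown. The Adverse events section does not say that its two routes are the only ones, nor does the Statistical analysis section say that the rank test is the only display. This limits the point to what the article does state. But it states a capture route and a comparison with its time point, and neither reaches on-treatment laboratory values. A later analysis plan can add a table, but it cannot easily make an ungraded result a recorded event.

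**Such toxicity would not go unseen.** A reader might infer that it would, and the document does not support that. Tests are done at every visit, a DSMB monitors safety (Ethics), and the interim analysis covers safety as well as futility and efficacy. Individual cases may well be noticed. However, the interim look comes at about two thirds of enrolment, the stopping rule it mentions concerns futility, and nothing stated turns a noticed value into a count by arm.

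**The trial is not designed to show safety.** This stands. Study design names efficacy and mechanism as the aims, and the safety claim appears only in the Discussion. For the kidney-deficiency mechanism a between-arm test of shift is a reasonable choice. The objection is to leaving it as the only stated comparison behind a safety claim. Nor is it a comparison of average changes, because it works on ranks.

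**The gain depends on the background rate.** This also stands. Both arms receive taxanes and/or anthracyclines, and with abnormalities in about 20% of both arms a count comparison does little better than the rank test.

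**The final assessment may not be the same visit for every indicator.** Table 1 last measures the kidney-deficiency indices at Visit 4, so for those the final value cannot be the follow-up visit. Blood counts and liver and renal tests do have a follow-up value. Even if Visit 4 were meant throughout, Visits 1–3 would stay out of the comparison.

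**Conclusion.** The point holds in a limited form. As stated, the plan has no rule that counts, grades or compares by arm a symptom-free laboratory abnormality during treatment, and its one stated blood comparison uses a visit at least about seven weeks after the granules end. That part rests on the text and on three-week cycles alone.

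The low power, about 9% to 20% for 5% to 10% of one arm affected at 85 per arm (10% to 25% at 107), rests on assumed rates, on no such cases on placebo, and on the abnormality still being present at the analysed visit. It should not be read as applying to abnormalities that chemotherapy commonly causes, such as neutropenia.

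The consequence is that a conclusion of safety would not be supported by the stated rules. Nothing in the document shows that the product is harmful or that cases would be concealed. The change is worth making because it is cheap and uses samples already planned.

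**What to change.** 1. **Adverse events section:** state that blood counts and liver and renal results from Visits 1–4 are graded on the WHO toxicity criteria that the Subjects section already names for eligibility, and that worsening from baseline is recorded as an adverse event whether or not the patient reports symptoms.
2. **Statistical analysis section:** report by arm the number of patients at each worst on-treatment grade, as a shift from baseline, for ALT, AST, Cr and blood counts. Give the difference in proportions with its confidence interval, so that a small number of cases is not judged by a p-value alone.
3. **Rank sum test:** keep it as a descriptive or mechanism analysis, and name the visit used for each indicator, since Table 1 does not measure all of them at follow-up.

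The cost is protocol wording, one grading field on the case report form and one table. No extra samples are needed. There will be more adverse-event entries, many caused by chemotherapy, for which the placebo arm provides the comparison. The benefit is mainly for abnormalities uncommon on placebo, such as marked ALT or creatinine rises, and small for common ones.
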